### 2.6 PK from six volunteers

In addition to validating the method for the detection and quantification of naproxen and its metabolite, 6-O-desmethylnaproxen, the PKs of six volunteers who will take one pill of naproxen (500 mg) and naproxen associated with esomeprazole (500 mg + 20 mg) will be investigated.

This study was registered as a clinical trial at ClinialTrials.gov (NCT030902193) after the analysis carried out by the website, as when prescribing these two drugs (naproxen alone and naproxen in combination with esomeprazole), a series of side effects may occur in a small portion of the population, such as allergies, gastric irritation, intestinal irritation, gastritis, colitis, and gastrointestinal bleeding. Such reports will be noted and analyzed during the clinical trial.

### 2.7 Analytical validation

The methodology for analyzing naproxen and 6-O-desmethylnaproxen in human saliva samples will be validated for essential parameters, such as residual effect and matrix effects, calibration curve, selectivity, precision, accuracy, stability, and dilution in accordance with the current guidelines of the United States Food and Drug Administration (October 2018) for bioanalytical methods to ensure reliability of the results obtained from the PK assays in human saliva.

Quality controls (QCs) for human saliva will be prepared by the addition of the final working solutions of treatment saliva to drug-free human saliva. Based on the lower limit of quantification (LLOQ), low-quality control (LQC), medium-quality control (MQC), and high-quality control (HQC) samples will be prepared. The QCs will be prepared, aliquoted (400 μL enriched saliva) in polypropylene tubes, and stored at −20°C until analysis. For residual effect evaluation, injections of the blank sample before and after the injection of the HQC sample will be analyzed. The chromatogram of the white sample obtained after HQC injection will be compared with the sample chromatogram of the LLOQ. The residual effect will be considered absent when the areas of interfering peaks eluted in the retention time of the analytes are less than 20% of the LLOQ and less than 5% of the IS area.

The matrix effect in the saliva will be evaluated using samples from six drug-free volunteers. Blank saliva samples from healthy volunteers will be obtained from the Laboratory of Clinical Pharmacology and Physiology, School of Dentistry, Bauru/USP. The matrix effect will be determined by comparing the peak areas obtained from naproxen, 6-O-desmethylnaproxen, and IS directly to the mobile phase (no matrix) with the peak in the presence of a matrix (white samples added to standard solutions of naproxen, 6-O-desmethylnaproxen, and IS after extraction). The normalizing factor of the IS in the matrix will be calculated for each sample matrix by dividing the ratio of the analyte by the response of the IS in the absence of the matrix. The coefficient of variation for the normalized IS must be less than 15%. Samples will be analyzed between the LQC and the HQC.

The saliva calibration curve will be prepared using the following concentrations in polypropylene tubes: 2500, 1250, 625, 312.5, 156.2, 78.1, 39.1, 19.5, 9.8, 4.9, and 2.4 ng/mL of naproxen and 6-O-desmethylnaproxen, plus a blank sample (no analyte and no IS) and a zero sample (IS only). Linear regression equations and correlation coefficients will be used from the ratios of the standard peak areas: IS plotted against the saliva samples used. Calibration curves will be plotted using the various concentrations of the IS versus the respective areas of their peaks, plotted as a linear regression line. Calibration curves will be approved when deviations of at least 75% of the calibration standards are less than or equal to 20% for LQC and 15% for other standards.

The LLOQ is defined as the lowest concentration of naproxen and 6-O-desmethylnaproxen quantified in saliva with acceptable precision and accuracy. The analyte interfering peaks at the retention time should be <20% of the analyte in the samples. To obtain the LLOQ, samples with the lowest detected concentration of naproxen, 6-O-desmethylnaproxen, and the IS in saliva will be evaluated ten times.

Three calibration curves for the analysis of naproxen and 6-O-desmethylnaproxen will be performed using aliquots of 400 μL of saliva containing a blank sample (no drug and no IS), one processed (IS added), and eight enriched with 25 μL standards of naproxen, 6-O-desmethylnaproxen, and IS, subjected to extraction and analysis procedures. The linearity will be evaluated using a linear mathematical model using the weighted equation 1/χ2.

Accuracy and precision will be evaluated in a single assay (intra-assay) and three different assays (inter-assay, in three different periods). Five replicates of each assay were used for LLOQ, LQC, MQC, and HQC. Precision is expressed as a coefficient of variation (%) and accuracy by relative standard deviation (RSD), which must be between 15% and 20% (more tolerant) of the nominal value.

Naproxen and 6-O-desmethylnaproxen stabilities in saliva were measured using the LQC and HQC, analyzed in triplicate after preparation, and stored under different conditions (after short-term stability, post-processing stability, and three cycles of freezing and thawing). The concentrations of the samples will be interpolated with a recently prepared calibration curve. Samples will be considered stable when concentrations are within 15% of the nominal value. Additionally, samples in saliva will be added to create a concentration greater than the calibration curves for naproxen and 6-O-desmethylnaproxen. Then, this will be diluted five times to obtain a dilution integrity QC (DQC).

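### Accuracy is defined by relative standard deviation, which is precision under another name, so the accuracy runs as written contain no test of bias from nominal.

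*Protocol article*

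**What the plan says.** All the relevant rules stand in section 2.7 (Analytical validation) of the protocol article.

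- **Precision:** "Precision is expressed as a coefficient of variation".
- **Accuracy:** "accuracy by relative standard deviation (RSD), which must be between 15% and 20% (more tolerant) of the nominal value".
- **Replication:** "Five replicates of each assay were used for LLOQ, LQC, MQC, and HQC", both within one assay and across three assays.
- **Calibration curve:** the condition for accepting it is "deviations of at least 75% of the calibration standards are less than or equal to 20% for LQC and 15% for other standards". Elsewhere, section 2.7 introduces LQC as the low quality control, not as a calibration standard.
- **Stability (LQC and HQC, in triplicate):** "Samples will be considered stable when concentrations are within 15% of the nominal value".

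The LLOQ is defined as the lowest concentration whose precision and accuracy are acceptable, so it depends on the accuracy rule. The section also says that validation follows the October 2018 guidance of the United States Food and Drug Administration. The text of that guidance is not part of the document.

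**The concern.** Accuracy asks how far the average reading lies from the known concentration. Precision asks how far replicate readings scatter around their own average. If both are judged by SD/mean, scatter is judged twice and bias not at all.

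Two further faults sit beside this one. The limit is written with a lower as well as an upper figure, and nothing says which QC level gets the 20%. The calibrator rule does attach its 20% to a level, but to one that is not a calibrator.

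Validating the saliva method is a stated purpose of the study (sections 1 and 2.6), and every concentration in the pharmacokinetic analysis passes through this assay. An undetected bias would shift the reported AUC, clearance and volume.

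**Working it through.** The plan gives a rule here and no computed figure, so there is nothing to reproduce. The check is whether the rule can respond to bias.

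**Inputs from section 2.7:** five replicates per level; four levels (LLOQ, LQC, MQC, HQC); limits of 15% and 20%. **Assumed inputs:** the assay's true bias and CV, because the document gives neither.

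**Formulas**

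- RSD = CV = 100 × SD / mean
- Relative error, RE = 100 × (mean − nominal) / nominal

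**Step 1: RSD does not change under proportional bias.** Take 97, 99, 100, 101, 103 against nominal 100. The squared deviations sum to 20, so SD = √(20/4) = 2.24, RSD = 2.24% and RE = 0%. Multiply every reading by 1.4: mean 140, SD 3.13, RSD = 3.13/140 = 2.24%, RE = +40%. The RSD is identical.

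**Step 2: an assay with 40% bias and CV 5%, one set of five.**

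- RSD exceeds 15% roughly when a chi-square on 4 df exceeds 4 × (15/5)² = 36. That tail is e^(−18) × (1 + 18) ≈ 3 × 10⁻⁷, so the set almost always meets RSD ≤15%.
- Reading 40% low: the mean is 0.60 of nominal and its standard error is 0.05 × 0.60/√5 = 0.0134. The ±15% limit at 0.85 is 0.25/0.0134 ≈ 19 standard errors away.
- Reading 40% high: the standard error is 0.05 × 1.40/√5 = 0.0313, and the limit at 1.15 is 0.25/0.0313 ≈ 8 standard errors away.

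Either way the set almost never meets a ±15% bias limit.

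**Step 3: range of assumed values.** Simulation of 200,000 sets of five normal replicates; share of sets that meet each limit:

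| True bias | True CV | RSD ≤15% | RSD ≤20% | abs(RE) ≤15% | abs(RE) ≤20% |
|---|---|---|---|---|---|
| 0 | 5% | 100% | 100% | 100% | 100% |
| 0 | 10% | 93.5% | 99.7% | 99.9% | 100% |
| +30% | 5% | 100% | 100% | 0% | 0% |
| +30% | 10% | 93.7% | 99.6% | 0.5% | 4.3% |
| +50% | 5% | 100% | 100% | 0% | 0% |
| +50% | 10% | 93.5% | 99.6% | 0% | 0% |

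The RSD columns depend on the CV and, apart from simulation error, not on the bias. Dividing the SD by nominal instead of by the mean does not help: with +50% bias and CV 5%, 99.7% of sets still meet a 15% limit.

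**Step 4: do the other rules cover the gap?**

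| Rule | What it constrains | What it leaves open |
|---|---|---|
| Stability | Deviation from nominal at LQC and HQC, after storage | LLOQ, MQC, inter-assay bias |
| Calibration curve | Deviations of at least 75% of the calibrators from a curve fitted to those same calibrators | Independent QC samples at any level |
| Accuracy | SD/mean only | Bias at all four levels, within and between assays |

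**Step 5: consequence of a constant factor k in every concentration.** Paired differences and their SD are both multiplied by k, so the paired t statistic in section 2.8 does not change. The half-life does not change either. AUC is multiplied by k; Clt/F and Vd/F are divided by k. With k = 1.4, AUC is 40% too high and Clt/F and Vd/F are 1 − 1/1.4 = 29% too low. With k = 0.6, AUC is 40% too low and both are 1/0.6 − 1 = 67% too high.

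**The case against.** The best defence is that this is a slip in naming. The sentence sets its limit at "which must be between 15% and 20% (more tolerant) of the nominal value". The reference to nominal suggests that the authors had deviation from nominal in mind and gave it the wrong name. This is plausible, but the statistic named is RSD, no other is defined, and anyone who scores the runs as written would compute SD/mean. Citing outside guidance does not cure that, because the article goes on to state its own criterion.

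A reader might also draw two stronger conclusions. The document does not support either of them.

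- **That a good assay would fail.** Read literally, a 15% to 20% band would reject almost every set from an unbiased assay with CV 5% and pass only about 6% of sets at CV 10%. But calling 20% the more tolerant figure makes sense only if both numbers are upper tolerances, and the calibrator and stability rules are worded as upper limits. The band is poor drafting; it is unlikely to be the intended rule.
- **That a badly biased assay would pass validation as a whole.** An assay 40% off at LQC and HQC would meet the RSD rule but break the 15% stability rule at those two levels. The figures above describe one set of five replicates under one rule and are not probabilities of passing validation.

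It is also fair to say that the study's only planned test compares the same volunteers on two treatments, where a constant proportional bias largely cancels. That limits the harm to the comparison but not to the absolute parameters. Bias that varies with concentration or between assays need not cancel.

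**Conclusion.** The accuracy criterion is wrong as written. This is a faulty acceptance rule, not detail left to a fuller document. RSD repeats the precision measure, so the accuracy runs contain no test of bias at the LLOQ, LQC, MQC or HQC. After allowing for the stability rule, the uncovered part is bias at the LLOQ and MQC and bias between assays. The LLOQ matters most, because its definition rests on the accuracy criterion.

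The size is conditional. With an assumed bias of 30% to 50% and CV of 5%, a set of five meets RSD ≤15% essentially always and a ±15% bias limit essentially never. Whether the assay has any such bias cannot be known from the document. If it does, and the bias is a constant proportion, AUC, Clt/F and Vd/F are affected while the paired comparison is largely spared.

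The band wording, the unassigned 20% and the naming of LQC in the calibrator rule are lesser faults that the same edit can correct.

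**What to change.** Amend section 2.7 as follows.

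1. Define accuracy as 100 × (mean measured − nominal)/nominal, reported for each of LLOQ, LQC, MQC and HQC, both intra-assay and inter-assay.
2. State 15% as an upper limit on its absolute value, with 20% at one named level only. The LLOQ, as the lowest level, is the natural candidate. The document does not assign it, so the authors should confirm the choice against the guidance they cite.
3. Keep CV as a separate upper limit for precision.
4. In the calibrator rule, replace LQC by the lowest calibration standard.

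The cost is wording and a re-scoring of the same five replicates per level. No extra samples or runs are needed, and validation data already in hand can be scored the same way.

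### The intra- and inter-assay accuracy rule uses RSD, which repeats the precision CV and cannot detect bias, and its 15% to 20% limit is worded as an interval with no QC level attached

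*Protocol article*

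**What the plan says.** All of this is in section 2.7 of the protocol article, Analytical validation.

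- Precision: "Precision is expressed as a coefficient of variation" in percent.
- Accuracy, in the same sentence: "accuracy by relative standard deviation (RSD), which must be between 15% and 20% (more tolerant) of the nominal value".
- Design: one run for the intra-assay assessment and three runs for the inter-assay assessment. "Five replicates of each assay were used for LLOQ, LQC, MQC, and HQC".
- LLOQ: "The LLOQ is defined as the lowest concentration of naproxen and 6-O-desmethylnaproxen quantified in saliva with acceptable precision and accuracy". The lowest-concentration samples are to be measured ten times.
- Calibration standards: a curve is approved if at least 75% of its standards deviate by no more than 20% (for LQC) or 15% (for the others).
- Stability: LQC and HQC, in triplicate, count as stable if they are no more than 15% away from nominal.
- Purpose: validation follows the FDA bioanalytical guideline of October 2018, "to ensure reliability of the results obtained from the PK assays in human saliva".

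**The concern.** Accuracy asks whether the mean result sits at the known concentration. Precision asks how far replicates scatter around their own mean. The plan gives both jobs to the same dispersion statistic, so an assay that reads consistently high or low can satisfy the accuracy rule.

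Two further faults sit in the limit itself. It is phrased as a range to fall inside, not as a ceiling. It also does not say which QC level may use the more tolerant figure.

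Validating the assay is one of the study's stated aims, and the LLOQ is defined through acceptable accuracy. Section 2.5 then reports AUC, Clt/F and Vd/F on an absolute scale, and these carry any proportional error in the measured concentrations.

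**Working it through.** **Inputs.** From section 2.7: five replicates per level per run, three runs, four QC levels, and limits of 15% and 20%. The document gives no assay CV or bias, so the values used here (CV 5%, 10%, 17%; bias 0, +30%, −30%) are assumptions chosen to show the range. The plan states no figure to reproduce.

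**Step 1: algebra.** RSD = CV = SD/mean. If every result is multiplied by (1+b), SD and mean are both multiplied by (1+b) and the ratio does not change. RSD therefore carries no information about proportional bias.

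An additive offset does change RSD, but only through its denominator. With SD 0.05 and nominal 1.00, an offset of +0.30 gives 0.05/1.30 = 3.8%, and an offset of −0.30 gives 0.05/0.70 = 7.1%. Both are well under 15%.

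**Step 2: pass probabilities for five replicates.** Treating the mean as known, 4 × (observed SD/true SD)² follows a chi-square distribution with 4 df, for which P(X ≤ x) = 1 − e^(−x/2)(1 + x/2).

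- CV 10%, ceiling 15%: x = 4 × (15/10)² = 9, P = 1 − e^(−4.5) × 5.5 = 0.94.
- CV 17%, ceiling 15%: x = 4 × (15/17)² = 3.11, P = 0.46.
- CV 17%, ceiling 20%: x = 4 × (20/17)² = 5.54, P = 0.76. The literal 15% to 20% interval then has probability 0.76 − 0.46 = 0.30.

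Simulation (200,000 normal samples of five per row) agrees:

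| Assumed CV | Assumed bias | RSD ≤15% | RSD from 15% to 20% | Mean within 15% of nominal |
|---|---|---|---|---|
| 5% | 0 | 1.00 | 0.00 | 1.00 |
| 5% | +30% | 1.00 | 0.00 | 0.00 |
| 5% | −30% | 1.00 | 0.00 | 0.00 |
| 10% | 0 | 0.94 | 0.06 | 1.00 |
| 10% | +30% | 0.94 | 0.06 | 0.005 |
| 10% | −30% | 0.94 | 0.06 | 0.00 |
| 17% | 0 | 0.46 | 0.30 | 0.95 |
| 17% | +30% | 0.46 | 0.30 | 0.06 |
| 17% | −30% | 0.46 | 0.30 | 0.002 |

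Both RSD columns are the same whatever the bias; only the last column responds to it. Pooling 15 replicates over three runs, with no between-run variance assumed, does not help. At CV 10%, RSD ≤15% passes with probability 0.99 at all three biases.

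**Step 3: a charitable reading.** Suppose the reference to nominal means SD divided by the nominal concentration. At CV 5%, the probability of staying within 15% is still about 1.00 at bias 0, +30% and −30%. Changing the denominator does not turn a dispersion measure into a test of bias.

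**Step 4: what the other checks cover.** Stability compares measured with nominal concentration, but only at LQC and HQC, in triplicate, and with the aim of finding storage loss. LLOQ and MQC are outside it. The calibration check looks at residuals of the points that fit the curve, so a proportional error common to all standards is absorbed by the slope. It also tolerates failures. With eight standards, 75% is 6, so two may fail. With the eleven concentrations also listed, 75% is 8.25, so nine must comply and again two may fail.

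**Step 5: consequence for the PK results.** A constant bias b multiplies AUC by (1+b) and Clt/F and Vd/F by 1/(1+b). At +30% the factors are 1.30 and 1/1.30 = 0.77; at −30% they are 0.70 and 1/0.70 = 1.43. Terminal slope, and so half-life, does not change. In the paired t-test every difference and its SD are scaled by the same factor, so t does not change. A bias that varies with concentration does not cancel in this way. It alters the terminal slope and the extrapolated area, and therefore t1/2 and AUC to infinity, which depend on low late concentrations in sampling that runs to 96 h.

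**The case against.** The best defence is that this is a slip in a condensed sentence. The mention of nominal and of a more tolerant figure suggests that deviation from nominal was meant, with 15% and 20% as two ceilings. The calibration rule uses the same pair as ceilings, and the section commits to a regulatory guideline that names the governing standard.

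Much of this stands for the limit. A reader might infer that a tight assay, say 5% RSD, would be rejected. That follows only from the literal interval, and the surrounding text points to a ceiling. It is a wording fault, not a likely outcome.

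A reader might also infer that bias is never tested. The documents do not support that. Stored LQC and HQC samples with a 30% error would fail the stability limit, and calibration standards have deviation limits of their own.

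Nor do the documents support the inference that the treatment comparison is undermined. A constant proportional bias shared by both periods leaves the paired t-test as it was.

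The defence does not rescue the statistic. The sentence names RSD explicitly, and a general reference to a guideline, whose text is not at hand, does not undo a specific rule. The reader also cannot work out which level gets 20%. The accuracy sentence names none, and the calibration rule attaches its 20% to LQC.

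**Conclusion.** The point holds in a limited form. The intra- and inter-assay accuracy criterion at LLOQ, LQC, MQC and HQC, as defined, does not test bias. The exposure is greatest at LLOQ and MQC, where no stability check applies, and at the LLOQ in particular because its definition depends on acceptable accuracy.

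The insensitivity to proportional bias is algebraic and needs no assumption. The pass probabilities rest on assumed CVs and biases and on normal errors; they illustrate the rule and do not predict error in this assay. What is at risk is the validation claim and the absolute AUC, Clt/F and Vd/F, plus t1/2 and AUC to infinity if bias varies with level. The statement that the paired comparison is unaffected assumes a bias that is constant over concentration and equal in both periods.

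**What to change.** Replace the sentence with two separate rules, both with upper limits:

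- Precision: CV no greater than 15%.
- Accuracy: 100 × (mean measured − nominal)/nominal, within ±15%.

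Apply both at each of LLOQ, LQC, MQC and HQC, within each run and across the three runs. Apply the same accuracy statistic to the ten LLOQ replicates.

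Name the one level at which 20% replaces 15%. The LLOQ is a plausible candidate, but that is an assumption. The sponsor should state the level and reconcile it with the calibration rule, which gives 20% to LQC.

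The cost is a short rewording and a recalculation on replicates already planned. No new measurements are needed. The only downside is that a biased assay would be seen to fail.

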### 2.8 Statistical analysis

After analyzing the PK and pharmacodynamic results using the Phoenix WinNonlin software (version 8.1), the data will be organized descriptively and a paired *t-*test will be performed to compare naproxen absorption after volunteers are administered, at two different times, naproxen alone or naproxen in combination with esomeprazole.
